### Stepped-Wedge Design

We use a stepped-wedge design, a type of cluster randomized trial that involves clusters (such as groups of clinics or schools) randomly assigned to different time points (ie, waves) to begin receiving the intervention [31]. The rationale for the stepped-wedge design includes its effectiveness in testing health care delivery models and related outcomes for systems of care, particularly when randomization at the individual level is not feasible [32]. A stepped-wedge design is also ideal when an intervention must be rolled out gradually due to logistical, financial, or ethical constraints, ensuring that all groups eventually receive the intervention. It is particularly useful for evaluating complex, systemic, or behavioral interventions when simultaneous initiation of the intervention is not feasible. Because the goal is to offer the intervention to all youth and caregivers at participating study sites, 2 clusters—consisting of 5 schools and 5 primary care clinics per wave**—**are randomly assigned to 2 different implementation waves. All clusters begin in the control condition, with the Connected for Wellness mobile app intervention introduced to schools and clinics at predetermined time points. By the end of the trial, all clusters will have received the intervention, allowing for a stepped implementation across the sites. Stepped-wedge designs are becoming increasingly popular for testing health care delivery models [33] and are an innovative approach for evaluating the public health impact of mobile apps delivered as universal or tier 1 interventions in youth- and family-serving systems of care [34].

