### Primary Outcomes: Cascade-of-Care Framework

The primary study outcomes are based on the cascade-of-care framework that focuses on population-level health needs and tracks individuals across relevant stages of a health care continuum [37,38]. Originally developed by the Juvenile Justice–Translational Research on Interventions for Adolescents in the Legal System [39,40], the steps in the cascade of care are identification of a behavioral health need, referral to behavioral health care, initiation of services, and engagement with services (>3 visits). The cascade of care has been adapted for youth in foster care [41]; this version was used for this study. Data on each step of the cascade of care will be obtained from deidentified electronic medical records and administrative data at the individual youth level from each of the study sites. This approach, which uses established databases, will enable comparison of cascade-of-care outcomes after implementation to data that were collected before preimplementation years. As detailed in the analytic plan in the Data Analysis section, individual-level data will be aggregated to the site level to test the hypothesis that implementation of the Connected for Wellness mobile app intervention is associated with improvements in youth progression through the cascade of care compared to the (preintervention) control condition. Improvements in the cascade of care are an established public health outcome as they help identify gaps in care and assess the effectiveness of the mobile app intervention. At a population level, in schools or primary care clinics, examining the cascade can inform how well an intervention improves youth access, engagement, and outcomes for a specific population and whether the intervention effectively addresses their unique needs and disparities. Statistical power was determined relative to the current level of each of the cascade outcomes (identification of mental health need, match to services, and initiation of services) in the sites as reflected in administrative data. Power was calculated separately for each cascade outcome. With a power of 0.8, an α value of .05, and 2-tailed tests, the planned design and sample sizes enable detection of small differences between the intervention and control conditions in all the cascade outcomes (2%-10%). Table 2 shows the operational definitions for the cascade-of-care outcome variables, and Table 3 shows the definitions, data collection, and outcomes.

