**Table 2 table2:** Cascade-of-care model based on Connected for Wellness triage outcomes.

Step	Rate	Operational definition
Youth at site (step a)	(a)	Total number of youth enrolled at a high school campus or on a patient panel at the primary care clinic site
Need identified (step b)	(b/a)	Subset of total enrolled youth (step a) who complete mental health and social determinant of health needs identification at school or the primary care clinic
Matched to services (step c)	(c/b)	Subset of youth with needs (step b) who receive a referral
Initiated services (step d)	(d/c)	Subset of those referred to services (step c) who initiate services (eg, first treatment session)
Engaged in services (step e)	(e/d)	Subset of those who initiate services (step d) who have ongoing sessions (≥3 visits)

**Table 3 table3:** Primary outcomes based on the cascade-of-care framework and covariates for generalized linear mixed model (GLMM) analysis.

Cascade step	Operational definition and data description	Covariates in GLMM
Need identified	Youth who completed self-assessments or were flagged by navigators	Age, gender, race, ethnicity, site type (school vs clinic), and urban or rural
Matched to services	Referral documented in site records or follow-up logs	All the aforementioned covariates+previous mental health history if available
Initiated services	Attended first mental health appointment	Same as the previous covariates
Engaged in services	≥3 treatment sessions attended	Same as the previous covariates+time since app onboarding

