The GLMM models will include county and intervention (vs control) as fixed effects, with site and youth as random effects. Study month will be treated as a continuous variable to account for potential secular trends. The primary focus will be on the intervention effect. For youth with mental health need, we will also examine time-to-event outcomes (eg, days to service initiation) using Poisson models with a log link function. If overdispersion is detected, we will use a negative binomial model. The relative risk ratio for intervention will indicate whether the app reduces time to service matching and initiation. To address heterogeneity, the GLMM will include random intercepts for sites and fixed effects for county and wave. We will test for interactions between intervention status and site characteristics (eg, urban vs rural and school vs clinic). We will also conduct stratified analyses by key demographic variables (race and ethnicity, age, and gender) to explore subgroup effects.

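### Days to matching and initiation are modelled as Poisson or negative binomial counts, which cannot handle youth with no event date, so unequal follow-up between conditions can produce a false app effect in either direction

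*Protocol article*

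**What the plan says.** The Data Analysis section of the protocol article fixes the population, the model and the reading of the result.

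- Population: "For youth with mental health need, we will also examine time-to-event outcomes".
- Model: "we will also examine time-to-event outcomes (eg, days to service initiation) using Poisson models with a log link function".
- Fallback: "If overdispersion is detected, we will use a negative binomial model".
- Reading: "The relative risk ratio for intervention will indicate whether the app reduces time to service matching and initiation".

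Table 2 defines the cascade steps as nested subsets. Matched youth are a subset of those with need, and initiation is defined as "Subset of those referred to services (step c) who initiate services (eg, first treatment session").

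On timing, the Stepped-Wedge Design section says "All clusters begin in the control condition, with the Connected for Wellness mobile app intervention introduced to schools and clinics at predetermined time points". The Primary Outcomes section says that using established databases "will enable comparison of cascade-of-care outcomes after implementation to data that were collected before preimplementation years". Results puts app deployment in August to September 2025 and preliminary analyses in October 2026. Objectives puts completion by June 2027. The article gives no control-window length, second-wave date, final data cut or follow-up cap.

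**The concern.** A Poisson or negative binomial regression with days as the response needs a finished number of days for each youth. The stated population includes youth who are never matched or never start, and youth who have not yet done so when the data are cut. For them there are only two options. Leaving them out restricts the comparison to completed waits, and the mean completed wait depends on how long each condition was observed. Entering their follow-up days treats the end of observation as the event. Either way the exponentiated coefficient mixes speed of access with length of observation.

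Unequal observation is plausible here, because every site receives the app last and control data come from earlier years. At stake is the stated conclusion that the app reduces time to matching and initiation: this model could support or contradict it for reasons unrelated to the app.

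**Working it through.** The article gives no figure for time to initiation, so there is none to reproduce. Its power statement covers the cascade outcomes only.

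**Inputs from the article.** First deployment is August 2025 at the earliest. October 2026 is 14 months later, about 425 days. June 2027 is 22 months later, about 670 days. These are the longest possible intervention windows at those two dates; second-wave windows are shorter by an unstated amount.

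**Assumptions.** No app effect; exponential waits with mean m of 45, 60 or 90 days; identification uniform over a window of T days; data stop at the end of the window; only completed waits analysed; control window 730 days; no study-month term; no clustering.

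**Formulas.** Available follow-up is uniform on (0, T).

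- Share completed: P = 1 − (m/T)(1 − e^(−T/m))
- Contribution of completed waits: N = [m − (T + m)e^(−T/m)] − (1/T)[2m² − (T² + 2Tm + 2m²)e^(−T/m)]
- Mean completed wait: N/P

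**Example, m = 60.**

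- T = 730: 50.14 / 0.918 = 54.6 days
- T = 670: 49.26 / 0.910 = 54.1 days; ratio 54.1 / 54.6 = 0.99
- T = 425: 43.12 / 0.859 = 50.2 days; ratio 50.2 / 54.6 = 0.92
- T = 180: 24.98 / 0.683 = 36.6 days; ratio 36.6 / 54.6 = 0.67

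**Null ratio of mean days, intervention to control (730-day control window; the true value is 1).**

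| Mean wait | 670 days | 425 days | 180 days |
|---|---|---|---|
| 45 | 0.99 | 0.94 | 0.75 |
| 60 | 0.99 | 0.92 | 0.67 |
| 90 | 0.98 | 0.87 | 0.55 |

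The 180-day column stands for a late second wave and is purely an assumption.

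**Reversed case.** With a 180-day control window and a 670-day intervention window, the same formula gives 1.33, 1.48 and 1.77 for means of 45, 60 and 90 days. A null app then looks slower.

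**Entering non-starters at their follow-up days.** Take a null simulation in which control youth are identified over 730 days and followed a further 425 days to the October 2026 cut, against a 425-day intervention window. At a median wait of 60 days the ratio is 0.76 among initiators and 0.80 with non-starters entered at follow-up time. If half of all youth never start, the second figure falls to 0.32.

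**Negative binomial.** In that scenario, with 300 youth per condition and analysing initiators, false rejection at medians of 60 and 120 days is 92% and 100% for negative binomial and 100% at both for Poisson. With equal 365-day windows the ratio is 1.00. Plain Poisson still rejects in 78% to 79% of runs from overdispersion, and negative binomial in 6% to 7%. So the fallback repairs the variance, not the bias.

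**Censoring-aware check.** Events per unit of person-time, which is Poisson on the event indicator with a log person-time offset, give null rate ratios of 0.998 to 1.002 in every simulated scenario and type I error of 3.5% to 5.8%. An equal 90-day window gives a null ratio of days of 1.00.

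**The case against.** **The wording may hide a valid model.** Poisson on an event indicator with a person-time offset handles censoring, and the term relative risk ratio could fit it. A full plan might contain it, along with a follow-up cap. That is possible, but the outcome is given as days, overdispersion is the named worry, and the ratio is read as a reduction in time, all of which point to a count of days. The two readings also run in opposite directions: a helpful app gives a ratio below 1 for days and above 1 for event rates. The problem is therefore what the text states, not a detail left to a later document.

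**A reader might infer that youth who never start are dropped.** The article does not say so. Their handling is unstated, and both available options are biased.

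**A reader might infer that the bias favours the app.** The order of conditions makes this plausible, but the dates needed to settle it are not shown. The study-month term also matters. A null simulation that adds it (initiators only, two waves, second-wave delay 0 to 365 days, mean waits 45 to 90 days, data to 425 or 670 days after first launch, fixed wave effect, no site effects) gives 1.10 to 2.07 if control follow-up stops at launch, and 0.77 to 1.10 if it runs to the final cut. The sign is not established.

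**A reader might infer that exposure is fixed at identification.** The article does not say how youth whose wait spans the launch are coded, so this cannot be charged as an error.

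**It is an additional analysis.** This stands. The primary cascade outcomes use binomial-logit mixed models and are untouched by this point.

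**Conclusion.** The point holds for the method: a count-of-days model is unsuitable for a population in which, by the protocol's own definitions, some youth have no event date, and the negative binomial fallback does not cure this. The resulting ratio cannot be read as a change in time to matching or initiation unless follow-up is equal between conditions.

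The size depends on facts not shown. Under the stated assumptions it is negligible for a 670-day intervention window against a 730-day control window (1% to 2%), a spurious reduction of 6% to 13% for 425 days, and 25% to 45% if a later wave has only 180 days. It reverses if control follow-up is the shorter. None of these is a forecast for this trial. Because the analysis is additional to the primary outcomes, the change should be made, but the trial's main conclusion does not hang on it.

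**What to change.** Replace the count-of-days model with a censoring-aware one that includes all youth with need and accounts for site clustering and calendar time. Suitable choices are Cox or discrete-time complementary log-log regression with a site random effect, or Poisson on the event indicator with a log person-time offset and a site random effect. Censor at the data cut or when the youth leaves the site. Split person-time at the site's launch so that intervention status varies with time. Report a hazard or rate ratio, and state that a value above 1 means faster matching or initiation.

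Alternatively, apply the same fixed follow-up window from identification in both conditions and count non-starters explicitly.

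The cost is analysis wording and modest programming. The same dates are used, and no new data are needed.

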## Abstract

**Background:**

Youth in the United States are experiencing rising rates of anxiety, depression, and other mental health challenges, yet many remain underserved due to systemic barriers such as poverty, limited access to care, and shortages in the mental health workforce. Schools and primary care clinics are trusted, community-based settings that offer strategic opportunities for early identification, prevention, and intervention. As part of a public health approach, integrating digital mental health tools into these settings can support broad access, enhance mental health literacy, and promote help-seeking behaviors among all students. When co-designed with youth and embedded within existing care systems, these tools offer a scalable, proactive solution to support well-being across diverse school-aged populations.

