### Data Analysis

Analyses will be conducted using the SAS statistical software (version 9.4; SAS Institute) [42]. Preliminary analyses will include examination of descriptive statistics, distributions, and internal consistency reliability of scaled measures. The primary hypotheses are that the Connected for Wellness mobile app will improve all cascade outcomes relative to the usual care control condition. Specifically, we hypothesize that the mobile app will affect site-level increases in the progression through the defined cascade of care, as defined in Table 2 (eg, youth at sites implementing the Connected for Wellness mobile app intervention will engage in more help seeking and be screened more frequently, and once screened and identified as needing mental health services, youth will be more likely to attend at least 3 sessions as compared to the control conditions [before implementation of the mobile app intervention]).

These hypotheses will be tested within a generalized linear mixed model (GLMM) framework implemented using the SAS PROC GLIMMIX statement. These models accommodate variously distributed dependent variables, including dichotomous outcomes such as those reflecting the cascade-of-care outcomes, and account for correlations among measurements of the same participants and nesting of youth within sites. Models will use a binomial distribution and a logit link function. All tests will be 2-tailed with a significance level of *P*=.05. For dichotomous outcomes, we will use a binomial distribution with a logit link function.

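### Time to service is analysed only in youth with identified need, a step the app is hypothesised to increase, so the intervention ratio cannot by itself show whether the app shortens time to care

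*Protocol article*

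**What the plan says.** In the protocol article, Data Analysis, the time outcome is introduced in one sentence: "For youth with mental health need, we will also examine time-to-event outcomes (eg, days to service initiation) using Poisson models with a log link function". A negative binomial model replaces the Poisson model if there is overdispersion. The result is given a causal reading: "The relative risk ratio for intervention will indicate whether the app reduces time to service matching and initiation".

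Who counts as having need is set out under Primary Outcomes: Cascade-of-Care Framework. Table 2 (step b) takes the enrolled youth "who complete mental health and social determinant of health needs identification at school or the primary care clinic". Table 3 gives the outcome definition as "Youth who completed self-assessments or were flagged by navigators".

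The same Data Analysis section hypothesises that the app improves all cascade outcomes, of which need identified (b/a) is the first. It adds that youth at sites with the app "will engage in more help seeking and be screened more frequently".

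No day 0 is given for the time outcome.

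**The concern.** The plan selects its analysis set by an event that follows implementation and that the intervention is expected to change. If the hypothesis about identification is right, the youth with need in app periods are not the same kind of group as those in control periods. They include youth who would have gone unidentified under usual care, and these may wait longer or shorter for a referral or first visit. The comparison of intervals is then no longer a comparison of like with like, whatever the randomisation of sites to waves achieved.

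A second mechanism depends on the clock. If days are counted from identification and the app moves identification earlier, the measured interval lengthens even when care starts on the same date.

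Neither problem is cured by the choice among Poisson, negative binomial and survival models, because both come from the set and the origin. At stake is the reading of the ratio: a true gain could be reported as no effect or as delay, or a gain could be overstated.

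**Working it through.** **The plan's own figure.** There is none to reproduce. The article gives no mean days, event count or power for the time outcome. Its power statement (0.8, α .05, two-tailed, differences of 2%-10%) covers the cascade outcomes only. All days and percentages below are assumptions for illustration.

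**What the ratio measures.** With a log link and a binary intervention term, the model estimates mean days under the app divided by mean days under control. A value below 1 reads as faster.

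**Step 1: change in who is analysed (applies whenever the set is youth with identified need).** Let e be the newly identified youth as a fraction of those who would have been identified anyway, and k their mean interval as a multiple of the others' mean. Nothing changes for the others. Then

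ratio = (1 + e × k) / (1 + e)

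| e | k = 0.5 | k = 1.5 | k = 2 |
|---|---|---|---|
| 0.10 | 1.05/1.10 = 0.95 | 1.15/1.10 = 1.05 | 1.20/1.10 = 1.09 |
| 0.25 | 1.125/1.25 = 0.90 | 1.375/1.25 = 1.10 | 1.50/1.25 = 1.20 |
| 0.50 | 1.25/1.50 = 0.83 | 1.75/1.50 = 1.17 | 2.00/1.50 = 1.33 |

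The ratio departs from 1 in either direction without any youth receiving care sooner or later than they otherwise would among those identified anyway.

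**Step 2: lead time (applies only if the clock starts at identification).** Let M be the control mean from identification to first visit, L the days by which identification moves earlier, and A the days by which care moves earlier. Then

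ratio = (M + L − A) / M

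With M = 60 (assumed):

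- L = 30, A = 0: 90/60 = 1.50
- L = 30, A = 15: 75/60 = 1.25
- L = 15, A = 0: 75/60 = 1.25
- L = 15, A = 30: 45/60 = 0.75

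The ratio exceeds 1 when L > A, equals 1 when L = A, and is below 1 when A > L.

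**Step 3: the same care dates from a fixed origin.** Assume that, under control, need is identified on day 90 and care starts on day 120 (interval 30 days), and that under the app care starts on day 90. From day 0 the ratio is 90/120 = 0.75. From identification it depends on when the app identifies need:

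| App identifies on day | Interval (days) | Ratio from identification | Ratio from day 0 |
|---|---|---|---|
| 75 | 15 | 15/30 = 0.50 | 0.75 |
| 60 | 30 | 30/30 = 1.00 | 0.75 |
| 45 | 45 | 45/30 = 1.50 | 0.75 |
| 30 | 60 | 60/30 = 2.00 | 0.75 |

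The same 30-day gain in care reads as a halving, no change, or a doubling.

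**The case against.** The strongest reply is that the plan does not say what the lead-time argument needs it to say. A reader might infer that the clock starts at need identification because the set is youth with need. That does not follow: restricting the set does not fix day 0. For initiation, the preceding step in Table 2 is referral, so the cascade itself does not point to a single origin. A condensed article may also leave the origin to the analysis plan, so its absence is no fault here. This stands, and the lead-time part is therefore conditional. Identification remains the most natural reading: referral cannot start the clock for time to matching, since it is the matching event, and app onboarding and site crossover do not exist in control periods.

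A reader might also infer that the plan predicts earlier identification, since the Abstract says that schools and clinics "offer strategic opportunities for early identification, prevention, and intervention". That sentence describes the settings, not a hypothesis about the app. The hypothesis concerns more frequent screening, and no shift in days is stated. App use is also anonymous while cascade data come from site records, so an in-app check-in need not set a date in a youth's record. Earlier identification is thus plausible through navigators and site screening, but it is not documented.

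Third, the interval from identification to service is a legitimate process measure that matches the conditional rates in Table 2, and increased identification is captured separately as b/a. That supports keeping the measure. It does not support the causal sentence attached to it.

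None of these replies removes the selection problem in Step 1, which needs no assumption about the clock.

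**Conclusion.** The concern holds in a limited form. The plan pairs a set defined by a step that the app is hypothesised to increase with a statement that the ratio will show the app's effect on time to matching and initiation. That pairing is stated in the article, so it is more than missing detail, and the claim is not warranted by the analysis described.

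The size cannot be derived from the documents. Under the assumed values, selection alone gives about 0.83 to 1.33. Lead time, if the clock starts at identification, gives 0.75 to 1.50 in the 60-day examples. The documents do not support saying that the app will look slower: the ratio falls below 1 when care moves forward by more days than identification, or when newly identified youth have shorter intervals.

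The point should be addressed but is not critical, because this is an additional analysis and the primary cascade outcomes do not depend on it.

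**What to change.** Base the claim about time to service on an analysis of all youth on the site roster or panel (Table 2, step a):

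- Start the clock at a date the app cannot move: the start of the school year or study period, or roster entry if later.
- Take first referral and first attended appointment as the events, and censor youth without an event.
- Treat intervention status as time-varying, changing at the site's crossover date, since a youth can be on the roster before and after it.
- Say in the text that the result is a rate of starting care, so that a ratio above 1 favours the app.

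Keep the identification-to-service interval as a process measure among identified youth. State its origin, and remove the sentence that reads its ratio as the app's effect on time to care.

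The cost is mainly wording in the analysis plan, with two downsides. The new result is a rate of starting care and not a waiting time, which is a different question. Availability of individual roster or panel dates must also be confirmed, because Table 2 defines step a only as a total number. If they are not available, use the period start for all youth.

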**Methods:**

This trial uses a stepped-wedge cluster randomized design across 20 community-based sites (10 high schools and 10 primary care clinics) in 2 counties in California. These counties were selected for their high proportions of underserved youth populations. All youth aged 13 to 22 years and their caregivers will be invited to access the app. Sites are randomized into 2 implementation waves. The app is introduced site-wide as a universal public health intervention supported by on-site navigators and peer ambassadors. The primary outcomes are derived from a cascade-of-care framework, including identification of mental health need, referral to services, initiation of services, and engagement (defined as ≥3 treatment visits). Data will be collected via anonymous in-app analytics, monthly World Health Organization–Five Well-Being Index assessments, and deidentified electronic health and administrative records. Generalized linear mixed models will be used to evaluate differences in cascade outcomes between pre- and postimplementation phases while accounting for clustering and site-level variability.

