### Limitations

The stepped-wedge design offers several advantages, including the ability to evaluate the intervention’s effectiveness while ensuring that all students in a high school or primary care clinic have the opportunity to access the wellness and prevention components of the app along with peer and family supports. It also allows for the assessment of temporal trends and the potential for learning or adaptation over time. However, this design also has limitations. The sequential implementation of the intervention may introduce biases such as those arising from differences in timing or external events affecting specific sites. Although the mobile app helps ensure fidelity by providing a standardized intervention across sites, the design still requires careful planning to manage logistical complexities and ensure consistency in implementation across diverse settings. Finally, variability in site readiness and capacity to implement the intervention highlights the need for robust support and ongoing monitoring of study sites. This includes tracking factors such as staff size, mental health service capacity, and the presence of existing peer-to-peer programs throughout the study.

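### The primary GLMM has no site-by-period variance component, so the intervention standard error is too small whenever sites drift differently over time; the size of the error depends on inputs the article does not give

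*Protocol article*

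**What the plan says.** The Abstract says "Sites are randomized into 2 implementation waves"; there are 20 sites (10 schools and 10 clinics), and all of them cross from control to the app.

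Data Analysis specifies a binomial-logit GLMM and gives its random effects twice. First: "The GLMM models will include county and intervention (vs control) as fixed effects, with site and youth as random effects". Then, as the stated answer to heterogeneity: "the GLMM will include random intercepts for sites and fixed effects for county and wave". Time enters once: "Study month will be treated as a continuous variable to account for potential secular trends". No site-by-period effect, site-specific time trend, decaying within-site correlation, random intervention effect or robust variance is named. The overdispersion fallback (negative binomial) follows the Poisson models for time to service and does not cover the binomial cascade models.

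The Primary Outcomes section says that "individual-level data will be aggregated to the site level to test the hypothesis", while Table 3 lists individual covariates such as age, gender and race. Limitations acknowledges that outside events may affect particular sites.

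**The concern.** A site intercept alone gives every pair of youth at a site the same correlation, however far apart in time they are observed. One shared month term removes a trend common to all sites but nothing that happens at one site in one period, such as a staffing gap, a local crisis or a change in referral capacity. Such a shock moves many different youth together, so a youth random effect does not absorb it either.

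Every site supplies both control and app data, and preimplementation years serve as the comparison, so the intervention contrast comes largely from change within sites. Site-by-period variance therefore enters its standard error directly. If it is present and not modelled, the intervals are too narrow and an app with no effect could be declared effective on a primary outcome.

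**Working it through.** **The plan's own figure.** Primary Outcomes states detectable differences of 2%-10% at power 0.8 and two-sided α .05. This cannot be reproduced, because the article gives no sample size, cluster-period size, baseline rate, ICC or CAC. For scale only: ignoring clustering, at assumed control rates of 10% to 50%, a 2-point difference needs 3,841 to 9,806 youth per condition and a 10-point difference needs 199 to 388.

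**Inputs.** From the article: 20 sites, 2 waves, a random intercept for site, wave as a fixed effect, two-sided 5% test. Assumed: 10 sites per wave crossing together, three periods, m youth per site-period, a 10% rate with outcome variance σ², nested-exchangeable truth, and a Gaussian approximation.

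**Formula.** The residual variance of a site-period mean is

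- in the stated model: σ²(1 − ICC)/m
- in truth: σ²(1 − ICC)/m + σ²·ICC·(1 − CAC)

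In this balanced layout, with wave fixed, the intervention estimate is entirely within-site. The ratio of true to model-based standard error is then

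R = √[1 + m·ICC·(1 − CAC)/(1 − ICC)]

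and the type I error is 2[1 − Φ(1.96/R)]. The assumed rate cancels out of R. A linear month term in place of categorical periods gives the same R.

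**Results.**

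| m | ICC | CAC | m·ICC(1−CAC)/(1−ICC) | R | Type I error |
|---|---|---|---|---|---|
| any | any | 1 | 0 | 1.00 | 5.0% |
| 50 | 0.01 | 0.95 | 0.025 | 1.01 | 5.3% |
| 37 | 0.02 | 0.95 | 0.038 | 1.02 | 5.4% |
| 75 | 0.02 | 0.95 | 0.077 | 1.04 | 5.9% |
| 20 | 0.05 | 0.9 | 0.105 | 1.05 | 6.2% |
| 37 | 0.05 | 0.9 | 0.195 | 1.09 | 7.3% |
| 75 | 0.05 | 0.9 | 0.395 | 1.18 | 9.7% |
| 300 | 0.02 | 0.95 | 0.306 | 1.14 | 8.6% |
| 750 | 0.05 | 0.9 | 3.947 | 2.22 | 37.8% |
| 1500 | 0.05 | 0.8 | 15.789 | 4.10 | 63.2% |

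The first row shows that the omitted variance is the sole cause: without it, the stated model is correct.

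**Monthly periods.** Over 24 assumed months with m = 50 per site-month and ICC 0.05, R is 1.06, 1.24 and 1.52 at CAC 0.95, 0.8 and 0.5. Coverage of the nominal 95% interval is then 93.5%, 88.7% and 80.2%. With m = 10 and ICC 0.01, R is 1.003 to 1.025. If the within-site correlation decays by month instead (factor 0.98 or 0.9), R runs from about 1.02 to 3.2.

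**Binomial-logit check.** A simulation under the null fitted a GLMM with site intercept, linear month, wave and county. It used 400 replicates, a base rate of 20% and a site SD of 0.5 on the logit scale. Type I error by site-month SD:

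| m per site-month | SD 0 | SD 0.1 | SD 0.2 | SD 0.3 |
|---|---|---|---|---|
| 10 | 5.8% | 3.5% | 7.0% | 6.3% |
| 50 | 5.5% | 7.8% | 9.0% | 15.0% |
| 100 | 6.0% | 5.5% | 12.8% | 23.8% |

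The Monte Carlo standard error near 5% is √(0.05 × 0.95/400) ≈ 1.1 points. Inflation appears with large site-months and larger site-month variation, and not clearly with small ones.

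**Which outcome is exposed.** R grows with m. In Table 2 the first rate (b/a) is taken over all enrolled or empanelled youth. The later rates (c/b, d/c, e/d) have successively smaller denominators, by an amount the article does not state.

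**The case against.** The strongest reply is that the size is unknown. Cluster size, ICC, CAC and period length are all missing, and with small denominators the test stays near its nominal level. That stands. A reader might take the 38% or 63% as the error rate to expect. The documents do not support this: those rows assume 750 and 1500 youth per site-period, come from a Gaussian approximation, and could fit only the first step. The simulation of the planned kind of model reached 23.8% at most, though with smaller site-periods.

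A reader might also cite the Limitations remark on "variability in site readiness and capacity to implement the intervention" as proof of omitted variance. It mostly describes differences between sites, which a site intercept can absorb. The remark on outside events at particular sites is the relevant one, and it makes such variance plausible without measuring it.

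It is tempting to call the youth effect unidentifiable. That would require one record per youth, whereas Data Analysis refers to repeated measurements on the same participants. Nor does the plan ignore effect heterogeneity: it tests interactions of the intervention with urban or rural location and school or clinic. These do not capture the remaining variation between sites.

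Finally, the wording does not say that no other random effect will be used, and degrees-of-freedom options usually belong in an analysis plan. But the article states the random effects twice and offers the site intercept as its answer to heterogeneity, so the structure is specified rather than left open.

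**Conclusion.** The concern holds in conditional form. As stated, the model understates the standard error of the app effect whenever site-by-period variance exceeds zero, and it is correct only if that variance is zero. The direction is certain; the size cannot be fixed from the article. Under the assumptions shown, inflation is slight for small site-periods with low ICC and serious for denominators in the high hundreds with ICC 0.05. Need identified (b/a) is therefore the most exposed outcome.

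The conflict between aggregating to site level and fitting youth random effects with individual covariates is real, but it is a separate inconsistency. A reader might infer that aggregation cures the variance problem or makes it worse. Neither follows: summing binomial counts within a site does not add a between-period component.

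**What to change.** - Add a random site-by-period intercept to the primary GLMM, define the period, and use a small-sample degrees-of-freedom correction suited to 20 sites.
- Add a random site-level intervention effect as a sensitivity analysis, if it is estimable.
- Recheck the 2%-10% detectable differences under this model. If they were derived without site-by-period variance, they scale by R: at R = 1.14, for example, 2 points becomes 2 × 1.14 ≈ 2.3.
- Keep the youth random effect only for outcomes with repeated records per youth.
- Reconcile Primary Outcomes (aggregation to site level) with Data Analysis and Table 3 (individual-level model), and name one unit of analysis.

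No extra data are needed; the model change is a line or two of code plus a degrees-of-freedom option. The price is wider intervals and possibly larger detectable differences. The new variance component may also be estimated near zero, in which case little is lost.
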